### **Data Confidentiality**

Paper-based records will be kept in a secure location and only be accessible to personnel involved in the study. Computer-based files will only be made available to personnel involved in the study through the use of access privileges and passwords. Prior to access to any study-related information, personnel will be required to sign statements agreeing to protect the security and confidentiality of identifiable information. Wherever feasible, identifiers will be removed from study-related information. Precautions are in place to ensure the data is secure by using passwords and encryption, because the research involves web-based surveys.

### **Subject Confidentiality**

Information about study subjects will be kept confidential and managed according to the requirements of the Health Insurance Portability and Accountability Act of 1996 (HIPAA). All PHI will be maintained on UPHS servers. Source documents are maintained in PennChart. No source documents will be printed or maintained in paper form at the study site. Data from PennChart will be recorded in Penn Medicine's REDCap system. The investigator and study team (which includes the research coordinator, and research assistants) will have access to PHI within PennChart and REDCap. We will label all PHI within REDCap as identifiable information so that de-identified exports are possible. All reports that include identifiable information will be stored on the Innovation Center secure drive, maintained behind the UPHS firewall. Once data analysis and manuscripts have been published, the databases will be removed from REDCap and the data will be de-identified on the secure drive. This de-identified dataset will be stored for up to five years after analysis is complete and manuscripts have been published. Once analysis is completed and any manuscripts are published, we will retain PHI no longer than seven years in accordance with government regulations, applicable policies, and institutional requirements.

### **Database Security/Protection Against Risk**

Information about study subjects will be kept confidential and managed according to the requirements of the Health Insurance Portability and Accountability Act of 1996 (HIPAA). All PHI will be maintained on UPHS servers. Source documents are maintained in PennChart. No source documents will be printed or maintained in paper form at the study site. To assure that patient, physician and other informant confidentiality is preserved, individual identifiers (such as name and medical record number/physician billing identifier) are stored in a single password protected system that is accessible only to study research, analysis and IT staff. This system is hosted on site at The University of Pennsylvania (UPenn) and is protected by a secure firewall. Once a participant is in this system, they will be given a unique study identification number (ID). Any datasets and computer files that leave the firewall will be stripped of all identifiers and individuals will be referred to by their study ID. The study ID will also be used on all analytical files.

The initial patient information collected for screening and recruitment will consist of name, address, phone number, demographic information such as race and income, and medication adherence practices. As our patient population is patients in the UPHS health system, the majority of this information will come from Electronic Chart reviews.

### **Sensitive Research Information**

This Research does not involve collection of sensitive information about the subjects that should be excluded from the electronic medical record.

### **Subject Privacy**

We will only interact with the subsample of subjects with which we plan to enroll in the study. With these subjects, we will conduct phone calls in a private area. When we call subjects, we will confirm the identity before beginning the recruitment process. When conducting the in-person 4-month visit, we will conduct blood pressure measurements and surveys in a private office location, with only one subject at a time.

### **Data Disclosure**

Blood pressure measurements will be disclosed to the subject's primary care physician if they reach or surpass a pre-established threshold determined to be an immediate danger to the subject's health.

### **Protected Health Information/Data Protection**

- Name
- Street address, city, county, precinct, zip code, and equivalent geocodes
- All elements of dates (except year) for dates directly related to an individual and all ages over 89
- Telephone and fax numbers
- Electronic mail addresses
- Medical record numbers
- Health Plan ID numbers

### **Consent Process**

#### **1.1 Overview**

We are requesting a waiver of the requirement to document consent and HIPAA authorization with a signature for participants enrolled into this study since we believe the research presents no more than minimal risk of harm to subjects and involves no procedures for which written consent is normally required outside of the research context. A majority of participants being enrolled in this study will be enrolled via a remote recruitment process, therefore we will read the IRB approved Consent/HIPAA script over the phone to each patient and ask them to provide verbal consent and verbal HIPAA authorization for use of their data in the study. Once a patient provides verbal consent, the research coordinator will select this option on the Consent/HIPAA screen on the participant dashboard that was just created for participation on the WTH health web platform for this study. At this point, the participant is randomized into 1 of the 3 study groups. After randomization the coordinator will inform the participant of their assignment and read the instructions for their study group. A copy of the consent form will also be mailed to the participant's home address. A copy of the Consent/HIPAA document will also be included in the recruitment mailings sent to all patients before being called by the study team. While we do ask that participants come for an in-person end of study visit, it is likely that due to attrition many will not

complete the final visit. As is such, we believe it impracticable to collect the signed consent form at this time, as we will end up with an incomplete record of written consent. Therefore, a waiver of the requirement to document consent and HIPAA authorization with a signature is requested.

#### 1.2 Children and Adolescents

Not applicable

#### 1.3 Adult Subjects Not Competent to Give Consent

Waiver of consent is being requested.

### **Waiver of Consent**

#### 1.1 Minimal Risk

The research presents no more than minimal risk of harm to subjects and involves no procedures for which written consent is normally required outside of the research context.

#### 1.2 Impact on Subjects Rights and Welfare

N/A

#### 1.3 Waiver Essential to Research

N/A

#### 1.4 Written Statement of Research

A copy of the Consent/HIPAA document will be included in the recruitment mailings sent to all patients before being called by the study team. After offering verbal consent to participate in the study, copy of the consent form will be mailed to the participant's home address.

### **Potential Study Risks**

As this study does not involve any medical decision making and only tests the use of social behavioral approaches to encouraging patients to use evidence-based treatments that their providers have prescribed to treat high blood pressure, we consider this study minimal risk. The primary risk would be from a breach of confidentiality involving medical records reviews and monitoring of hypertension medication and blood pressure adherence with text messaging which will be maintained on the Way to Health platform. This risk has been mitigated by extensive privacy protection protocols, a highly secure data storage system, and a plan to remove identifiers from the data wherever possible. In addition, all personnel will be held to high standards of upholding confidentiality and safeguarding patient privacy.

### **Potential Study Benefits**

The immediate benefits of this study for participants may include an improvement in adherence to medications that have been proven to be effective in improving patient outcomes. It is possible that the benefits for many participants will be minimal. However, as mentioned, we believe the risks are also minimal. Knowledge gained from the study will assist in development of interventions in other high risk patient populations in which non-adherence rates are high. The potential public health impact of a successful intervention to improve adherence to medications is great and could reduce the number of deaths from health related outcomes in the United States each year.

**Data and Safety Monitoring**

The study PI will be responsible for monitoring the data and safety of the study, and ensuring the ongoing quality and integrity of the research study. The investigator will permit study-related monitoring, audits and inspections by government regulatory authorities and University compliance officers.

**Risk/Benefit Assessment**

Medication adherence is an important factor contributing to poor control of a number of chronic diseases, including hypertension, hyperlipidemia, coronary artery disease, and diabetes. Many studies show that adherence to simple medication regimens is suboptimal with less than half of patients taking medications in the year after initial prescription. This study is designed to test an intervention that incorporates many components that have previously demonstrated improvement in past studies. We believe the combination of these approaches in this study will provide the research and public health communities with important information that can lead to broad generalizability in treating people at risk for the above mentioned chronic diseases and death nationally, as these types of interventions could be set up by healthcare systems to be broadly utilized.

# Final Protocol

**\*\*New changes from initial protocol notated in bold, parts removed from initial protocol notated in strikethrough**

## Abstract

A 3-arm randomized pilot trial aimed at comparing the effectiveness of different approaches to improving blood pressure (BP) control: A) remote monitoring of BP and medication adherence; B) remote monitoring of BP and medication adherence with feedback to social support; and C) usual care. The targeted population is patients aged 18-75 within the Penn Family Care practice with at least 2 visits within the prior 12 months with blood pressure readings exceeding recommended HTN guidelines.

## Study Instruments

All subjects will complete a baseline and post-intervention survey. The baseline survey will collect basic demographics and baseline medication adherence and blood pressure monitoring frequency. The post-intervention survey will collect ~~on~~ similar adherence and monitoring information, as well as qualitative data regarding patient perceptions about the interventions. **Provider interviews following the intervention period will collect clinician and care team perceptions about the interventions as well as feedback for improvement of future iterations.**

## Group Modifications

For subjects in the Control (usual care) arm of the study, the subjects will not receive text reminders to monitor their blood pressure or take their medication(s). For subjects in the Remote Monitoring plus Social Support (RM+SS) arm of the study, the subjects will receive additional feedback from a designated support partner.

## Administration of Surveys

All subjects will complete a baseline and post-intervention survey. The baseline survey will collect basic demographics and baseline medication adherence and blood pressure monitoring frequency and be conducted over the phone after the participant has been consented. The post-intervention survey will collect similar adherence and monitoring information, as well as qualitative data regarding patient perceptions about the interventions. The post-intervention survey will be completed at the in-person 4 month visit. These surveys should take no more than 15 minutes to complete. Demographic and socio-economic questions are modified from demographic questions on the Behavioral Risk Factor Surveillance System survey, administered by the Centers for Disease Control and Prevention. **Provider interviews following the intervention period will collect clinician and care team perceptions about the interventions as well as feedback for improvement of future iterations. Provider interviews should take no more than 20-25 minutes to complete.**

## Objectives

### 1.4 Objectives

We plan to leverage the Way to Health (WTH) platform to develop and evaluate a new HTN service-delivery model that is integrated with routine clinical care at Penn Family Care (PFC), an academic family medicine practice in West Philadelphia. Among patients with poorly controlled HTN:

3. We will assess the effects of monitoring blood pressure and medication adherence with feedback to the patient and to the clinical practice, as needed if out of control.
4. We will also compare the impact of providing feedback to a social support partner with what

we call facilitated cheerleading.

### 1.5 Primary Outcome Variable

The primary outcome is systolic blood pressure during the 4-month study visit by intervention arm, adjusting for the initial systolic blood pressure. For patients with missing data who do not complete the 4 month in-person blood pressure reading, we will conduct multiple imputation of the SBP values at 4 months as a function of baseline variables, including intervention arm.

### 1.6 Secondary Outcome Variable(s)

Secondary outcomes include the percent of patients that are normotensive during the 4 month study visit, estimation of recruitment and attrition rates, **and evaluation of patient perceptions about the intervention from surveys.** We will also compare medication adherence **by intervention arm** after enrollment, adjusted for BMI, age, gender, race, forgetfulness (from the baseline and follow-up surveys), and diabetic status. In addition, we will track BP measurements from the EMR that are obtained through usual care as well as during PCP visits, MPM messaging, and phone calls; **number of office visits** and hospitalizations; and medication changes for up to ~~9-38~~ months after the study intervention using similar models. We will analyze diastolic blood pressure at the 4-month visit, adjusting for the initial diastolic blood pressure. ~~Lastly, we~~ **We will measure and compare medication and blood pressure adherence between the two intervention arms, allowing us a more proximal metric to see if social influence makes a difference on adherence with texting. Lastly, we will evaluate qualitative data regarding provider experience with the intervention as well as feedback about how the intervention could be improved for future iterations. This data will be supplemented with information gathered from a review of provider actions following monitoring encounters.**

## **Background**

### 1.1 Program Goals

Hypertension (HTN) affects about 30% of US adults, and effective treatment that reduces long-term risk is available, but only about half of adults maintain good control. HTN control requires diagnosis, initiation of treatment, adherence to medications, and titration of medications. The traditional visit-based primary care model is inadequate to address management needs, given the limited visit time and lack of insight into the behavior of patients outside of the clinic setting.

Substantial literature has shown the benefit of remote monitoring interventions in controlling HTN, but the effects are not typically sustained and traditional primary care practices may not have the infrastructure to respond to remote monitoring data. There is an opportunity to develop automated approaches to monitoring blood pressure and medication adherence by leveraging principles of behavioral economics and clinical practice re-design. Our focus is on self-monitoring of blood pressure and medication adherence using bi-directional text messaging.

In addition to providing feedback to patients, we will also engage a friend or family member identified by the patient who has agreed to act as a feedback partner. Those with active social support typically have better clinical outcomes, and the feedback partner could serve as a witness to non-adherence as well as a cheerleader. Despite considerable enthusiasm for the concept that social support can be used to advance medication adherence, there is currently no evidence that this provides benefit beyond individual feedback. The tepid results from those few studies may be explained by limited participation of the feedback partner or an insufficient dose of cheerleading. There may be greater impact if we make it easier for them to communicate with the patient to provide motivation **through the use of opt-out messaging.**

We plan to leverage the Way to Health (WTH) platform to develop and evaluate a new HTN serve delivery model that is integrated with routine clinical care at Penn Family Care (PFC), an academic family medicine practice in West Philadelphia. Among patients with poorly controlled HTN, we will assess the effects of monitoring blood pressure and medication adherence with feedback to the patient and to the clinical practice, as needed if out of control. We will also compare the impact of providing feedback to a social support partner with what we call facilitated cheerleading.

Some health systems have employed a proactive approach to identifying eligible patients and encouraging participation in CRC screening through direct outreach, thereby eliminating barriers to screening such as the in-office visit. Kaiser Permanente Northern California is one such example that improved their screening rates to over 80% through mailed FIT outreach to eligible patients. The opportunity exists to extend this model to other health systems, such as UPHS, to engage in organized direct outreach with mailed FIT in order to enhance CRC screening rates.

In this study, we will be using population-based outreach screening to better understand mailed CRC screening uptake. By evaluating the effectiveness of opt out versus opt in mailed outreach screening, we will enhance the public health capacity, and efficiency, to increase CRC screening uptake and reduce preventable death from this disease. Default settings (such as opt out) have been effective in producing desired behavior actions in a variety of economic and clinical contexts, including employee enrollment in retirement savings, organ donation, subject enrollment in research studies and breast screening. However, there is a lack of evidence for use in CRC screening. Moreover, by furthering our understanding of patient-level facilitators and barriers to completing mailed FIT, we hope to support the need for further research to improve the delivery of CRC screening and screening uptake in diverse population groups.

## **Statistical Considerations**

### 1.1 Power and sample size

Assuming 5.3mmHg standard deviation of SBP (given variability of BP over time) and a two-sided significance level of 0.017 (to accommodate the three pairwise comparisons), our sample size of 60 in each intervention arm and 30 in the control arm provides 80% power to detect a difference in SBP reduction of 3.75 mmHg between either intervention and usual care, and a difference in SBP reduction of 3.1 mmHg between the remote monitoring and social influence arms. A preliminary data extraction shows about 2300 patients uncontrolled hypertensive patients in PFC, which should provide a sufficient population for enrollment. **However, based on additional clinical information obtained after the study was initiated, we estimate a standard deviation for change in SBP of 20mmHg, larger than our initial estimate. Thus, we increased our accrual target to 100 in each intervention arm and 50 in the control arm, which provides 80% power to detect a difference in SBP reduction of 11mmHg between either intervention and usual care, and a difference in SBP reduction of 9mmHg between the remote monitoring and social influence arms.**

### 1.2 Data analysis

**As is standard in a randomized controlled trial, we will conduct our primary analysis will follow the intention to treat approach, in which participants are analyzed according to their assigned treatment regardless of compliance. analysis.** For patients with missing blood pressure data, we will first include blood pressure readings available from the electronic health record (EHR) occurring from 90-150 days from the participant's start in the intervention, and then conduct multiple imputation using all available baseline covariates.

The primary ~~outcome analysis~~ will relate the systolic blood pressure ~~during~~ at the 4 month visit to **assigned** intervention arm, adjusting for the initial systolic blood pressure by including **the** baseline measures in the model. ~~For patients with missing data who do not complete the 4 month in person blood pressure reading, we will conduct multiple imputation of the SBP values at 4 months as a function of baseline variables, including intervention arm.~~

Secondary analyses include ~~modeling~~ **analyzing achievement** of normotensive ~~status~~ **by study arm** using logistic regression **and repeating the analyses for systolic blood pressure with diastolic blood pressure at the 4-month visit. We will** estimate ~~ion~~ of recruitment and attrition rates, and evaluate ~~ion~~ of patient perceptions about the interventions from follow-up surveys. We will also compare medication adherence **and blood pressure monitoring adherence** by intervention arm after enrollment. We will adjust these analyses for BMI, age, gender, race, forgetfulness (from the baseline and follow-up survey), and diabetic status. In addition, we will track BP measurements **by arm** from the (EHMR) that are obtained through usual care **for up to 8 months after the study intervention. We will** ~~as well as during~~ **also evaluate** PCP visits, MPM messaging, phone calls, hospitalizations, and medication changes. ~~for up to 8 months after the study intervention using similar models. Lastly we will analyze diastolic blood pressure at the 4-month visit, adjusting for the initial diastolic blood pressure.~~ **We will repeat all analyses by sub-group related to time of enrollment (round 1 and round 2). Finally, we will perform a thematic evaluation of provider perceptions about the interventions from information gathered during follow-up telephone interviews as well as process data collected from a review of provider actions following monitoring encounters.**

## **Study Design**

### 1.1 Design

This is a prospective, randomized controlled trial: ~~150-250~~ patients will be randomized into one of three intervention arms: A) remote monitoring of blood pressure and medication adherence; B) remote monitoring of blood pressure and medication adherence with feedback to social support; and C) usual care. Participants will be randomized in a 2:2:1 ratio to the three study arms in variable blocks of 5 and 10 using a computer-generated randomization algorithm. The investigators will be blinded to the randomization assignment. The research coordinator and research assistants will be unblinded. The blind may be broken in the case of an emergency.

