#### **Subject Recruitment**

Participants in this study will be identified via electronic medical records review by our study staff. The study staff will work with UPHS to create a filter for the electronic medical record system that will generate a ~~monthly~~ list of patients who may meet the study criteria. A study coordinator will review the list of patients to determine eligibility. If patients meet the minimal requirements they will be added to the study screening data base and contacted via recruitment letter and up to ~~3~~ **5** follow-up phone calls. If participants are interested, the coordinator will complete an intake form and consent via the remote enrollment process over the phone. The coordinator will enter patient information directly into the Way to Health web portal for this study. After providing consent, the patient will be randomized into 1 of the 3 study arms and will be read the script for that arm.

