## **follow-up telephone interviews.**

### **Procedures**

**Recruitment:** The study staff will work with UPHS and the Penn Data Store to create a filter for the electronic medical record system that will generate a ~~monthly~~ list of patients who may meet our study criteria. A study coordinator will review the list of patients to determine eligibility. If patients meet the minimal requirements they will be added to the study screening database and will be mailed a recruitment letter and informational brochure, followed by up to ~~three~~ **5** recruitment calls. During the recruitment phone call, a coordinator will ask the patient if they are interested in answering screening questions to confirm they are eligible to participate in this research study. If they are eligible, the coordinator will review the verbal consent/HIPAA script to the patient over the phone and obtain verbal consent and HIPAA authorization.

**Enrollment:** Enrollment will occur on the Way to Health platform for this study and patient information will be directly entered into the Way to Health website to create a participant study account. The patient will be mailed a copy of the consent document. After confirming consent to participate, the coordinator begins entering basic demographic information for the patient into the WTH site, including the name and contact information for a social support partner. All enrolled patients will receive a \$25 incentive for their initial participation in the study. The research coordinator will collect the SSN of all study participants to enter into the W-9 webpage on the Way to Health web portal for this study to facilitate participant incentive payment. Providing SSN is not mandatory for enrollment but it is mandatory for receiving payments. The coordinator will ask the participant to provide details about medications they have been prescribed. After a patient enrolls, a message will be sent to **a designated nursing pool** and their PCP via EPIC to notify their physician that their patient is enrolled in our study. Patients will be made aware of this message to their PCP in both the consent and enrollment process. **For patients in the intervention arms, this message will also include a pended procedure order authorizing patient submitted blood pressure measurements to be reviewed via a specially created flowsheet linking Way to Health to Epic.**

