**Randomization:** The coordinator will use the Way to Health web platform to randomize patients into this study. Patients will be randomized into 1 of the 3 study arms (ratio 2:2:1) in variable blocks of 5 and 10. After randomization occurs, the study coordinator will inform the patient of the randomization group they have been assigned into. Arms **A-1** and **B-2** will receive a blood pressure cuff and bidirectional text messaging regarding blood pressure and medication adherence. Arm **B-2** will also include a social support partner to participate. Arm **C-3** will receive usual care. After randomization occurs, the study coordinator will inform the patient of the randomization group they have been assigned into. Those patients assigned to Arms **A-1** and **B-2** (remote monitoring) will be shipped the blood pressure cuff with instructions for use and a number to call us with questions. If we do not receive blood pressure readings from the patient ~~5-10~~ days after the patient received the package, a coordinator will call the patient to make sure the device is working properly. The coordinator will also reach out to the feedback partner in the social support arm to include in Way to Health.

**Monitoring:** **Participants in Arms 1 and 2 will be asked to submit blood pressure measurements three times each week for the duration of the study. If at any point, 3 out of the last 10 reported BP measurements are elevated, the elevated measurements and any measurements between (up to 10, with a minimum of 5 if available), will be reported to the Nursing Pool PCP via a medical record encounter. This encounter will also reference the flowsheet so the care team may view all patient submitted measurements to date, if needed or desired. Information about self-reported medication**

adherence will also be reported ~~to the PCP~~ at this time. Nursing pool staff will meet twice weekly with an assigned Nurse Practitioner (NP) to review all monitoring notification sin bulk, and make appropriate medication adjustments with follow-up with the patient as needed. The final encounter will be routed by the nursing pool to the PCP as an FYI. Measurements will be reported again in this same manner if they remain elevated and 3 weeks have elapsed since last reported.

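### The unblinded coordinator who recruits and randomises can partly predict allocation, because the protocol prints the only two block sizes (5 and 10) and states no concealment of them

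*Supplement*

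**What the plan says.** Final Protocol, Study Design, section 1.1 Design, sets the scheme: "Participants will be randomized in a 2:2:1 ratio to the three study arms in variable blocks of 5 and 10 using a computer-generated randomization algorithm". Under Procedures, the Randomization paragraph repeats it: "Patients will be randomized into 1 of the 3 study arms (ratio 2:2:1) in variable blocks of 5 and 10". No stratification factor is given, and recruitment is from one practice.

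On blinding, section 1.1 Design says "The investigators will be blinded to the randomization assignment", and then "The research coordinator and research assistants will be unblinded".

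The steps around allocation belong to the coordinator role:

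- Screening (Subject Recruitment): "A study coordinator will review the list of patients to determine eligibility".
- Recruitment calls, up to 5, and consent (Procedures, Recruitment): "the coordinator will review the verbal consent/HIPAA script to the patient over the phone and obtain verbal consent and HIPAA authorization".
- Randomisation (Procedures, Randomization): "The coordinator will use the Way to Health web platform to randomize patients into this study".
- Disclosure: the same role then tells the patient the arm (Study Design, section 1.2 Consent Process, and Procedures).

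Section 1.2 also says that the arm is assigned only once verbal consent has been recorded on the platform. Nothing says that block sizes are withheld from recruiting staff, or that recruiters are kept from past assignments.

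**The concern.** A web platform hides the allocation list. It does not hide what can be worked out from earlier assignments by someone who knows the block sizes. For a 2:2:1 ratio, 5 is the smallest possible block and holds exactly one usual-care slot. With 5 and 10 as the only sizes, every block boundary falls on a multiple of 5.

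The person able to make this inference also influences who enters the trial, through persistence with calls and judgement on borderline charts. If usual care looks unlikely for the next slot, a more motivated patient might be pursued harder, even without intent. The primary model adjusts for baseline SBP. That would take out selection on baseline SBP but not selection on motivation or likely adherence, which is what this intervention acts on. The comparisons with usual care are the most exposed, because that arm has only 50 of the 250 patients.

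**Working it through.** **Inputs from the documents.** Ratio 2:2:1; block sizes 5 and 10; target 100, 100 and 50 (total 250); SD of SBP change 20 mmHg; two-sided alpha 0.017; stated power 80% for 11 mmHg (intervention v usual care) and 9 mmHg (between interventions).

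**Assumptions.** The documents do not give the mix of block sizes. I take 50:50, with a range from 25:75 to 75:25. The steering shift d (mmHg) has no source in the documents, so results are left in terms of d.

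**1. The plan's own figure.** The plan gives no figure for predictability, only for power. A normal approximation with SD 20 and alpha 0.017 gives 78.5% for 11 mmHg (100 v 50) and 78.7% for 9 mmHg (100 v 100). Both are close to the stated 80%. The standard error for intervention v usual care is 20 × √(1/100 + 1/50) = 3.46 mmHg.

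**2. How a block reveals itself.** Starting from a known boundary, the chance that the first five of a 10-block happen to be 2:2:1 is C(4,2) × C(4,2) × C(2,1) / C(10,5) = 6 × 6 × 2 / 252 = 28.6%. So about 71% of 10-blocks show themselves at the midpoint. The make-up of the second half and the next boundary are then known.

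**3. Predictability.** Permuted-block sequences of 250 were simulated. The guesser knows the two sizes and all past assignments, does not see the current block's size, and updates the exact probability of each next arm.

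| Scheme | Best guess right | Next arm certain | Usual care ruled out |
|---|---|---|---|
| No information | 40% | 0 | 0 |
| Fixed block of 5 | 61% | 24% | 40% |
| 5 and 10, 50:50 | 57% | about 7% (17 of 250) | about 14% (34 of 250) |
| 5 and 10, other mixes | 56–59% | 4–9% | 9–18% |
| 10, 15, 20, 25, 30 | 51% | about 1% (2 of 250) | about 2% (5 of 250) |

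Under 5 and 10 at 50:50, the guesser is at least 80% sure for about 19% of patients (48 of 250). Usual care itself is certain for only about 1%. If the guesser sees only half of past assignments, 47% of guesses are right and almost none are certain.

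**4. Possible bias in intervention v usual care.**

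- *Narrow steering.* Patients are shifted by d only when usual care is ruled out. All 34 such slots fall in the intervention arms: 34/200 = 0.17, so the bias is 0.17d. Across the other mixes, 22/200 to 45/200 gives 0.11d to 0.22d.
- *Full steering.* Every patient is shifted up or down by d whenever the probability of usual care departs from 20%, however slightly. The simulated bias is about 0.86d (0.80d to 0.91d across mixes).

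For an assumed d = 2 mmHg these are 0.34 and 1.7 mmHg. With critical value 2.387, the false-positive risk is Φ(−2.387 + b/3.46) + Φ(−2.387 − b/3.46), where b is the bias. It rises from 0.017 to 0.0175 under narrow steering and to 0.031 under full steering.

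**The case against.** The plan has real safeguards. The sequence is computer generated, block size varies, and the arm is released only after consent is recorded. Most eligibility criteria are objective (age, diagnosis code, BP thresholds, a texting phone, a prescribed drug). Charts are reviewed before the calls, when the eventual slot is not yet known. The protocol does not say that the coordinator picks the order of calls. The modifications log reports a smaller eligible pool than expected, which leaves less room to choose among patients.

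Much of this stands, and it limits three stronger readings that a reader might infer:

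- *That the coordinator will often know the next arm.* Certainty is reached for about 7% of patients, against 24% with a fixed block of 5. Varying the size removes over two thirds of the certain allocations, although the guess rate falls only from 61% to 57%.
- *That 57% is the expected guess rate.* It is an upper bound. It needs someone who tracks every assignment, whereas the plan names a coordinator and research assistants, and the log shows staff changes.
- *That a bias of about 1.7 mmHg should be expected.* That figure needs full steering and an assumed d of 2 mmHg. The documents support neither.

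The objection does not dispose of the point. Release after consent does not stop inference from past assignments, and up to 5 calls per patient leaves discretion over persistence. Investigator blinding does not help, because investigators are not described as recruiting.

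**Conclusion.** The point holds as a modest, avoidable weakness in allocation concealment. The unblinded role that recruits can predict the next arm better than chance, and the protocol publishes the sizes that make this possible without saying they are hidden. With full knowledge of past assignments and a 50:50 size mix, the upper bound is 57% correct guesses against 40%, about 7% certain, and usual care ruled out for about 14%. Incomplete knowledge lowers these figures.

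Bias is possible, not shown. Its size runs from about 0.17d to about 0.86d, where d is unknown and could be zero. The documents do not support a claim that the arms will differ through selection, or any particular bias in mmHg. The case for changing the scheme rests on its very low cost, not on a demonstrated error in the comparisons.

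**What to change.** In Study Design, section 1.1 Design, and in the Randomization paragraph under Procedures, replace the words that name the two sizes with:

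*randomly permuted blocks of varying size, generated in the Way to Health platform; block sizes are held by the platform programmer or statistician and are not disclosed to recruiting staff.*

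Put the actual sizes (several larger multiples of 5, for example 10 to 30) only in a restricted randomisation file. They should not be printed in the protocol, since that would repeat the problem. The change can apply only to participants still to be enrolled.

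The cost is a platform setting and a wording change, with no extra patients or staff. Balance is slightly looser: the final usual-care count would be about 47–53, and power for 11 and 9 mmHg changes by no more than about 0.1 percentage point. Predictability is reduced, not removed. Even if the new sizes became known, the guess rate would be about 51%, and the full-steering bias about 0.58d instead of 0.86d.
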